## 2 Methods and analysis

### 2.1 Aims and design

A prospective, single-blinded, randomized controlled trial (RCT) is currently being conducted in a monocentric setting in Austria. The aim is to investigate the effects of coordination exercises compared to standard physiotherapy, on balance and walking in patients who suffer from stroke-related ataxia.

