#### 2.3.2 Exclusion criteria

Exclusion criteria are a modified Rankin Scale (mRS) score of 5 or more (Rankin, 1957), a previous stroke leading to persistent debilitating neurological deficits defined as an mRS score of 3 or more, a comorbidity that limits active study participation (e.g., life expectancy of <3 months, alcohol or drug abuse), physical or mental conditions that would not allow safe participation in the study or would influence the assessment of outcomes (e.g., dementia, cardiac insufficiency, severe aphasia, etc.), or pregnancy.

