### 2.7 Statistical analysis

IBM SPSS software, release 29.0 (IBM Corporation, Armonk, New York, USA), R software version 4.3.2 (R Foundation for Statistical Computing, Vienna, Austria) and GraphPad Prism 10 (San Diego, California, USA) will be used for the data analyses. Descriptive statistics are used for the baseline demographic variables, primary and secondary outcomes. Continuous data is checked for significant outliers using studentized residuals and a normal distribution using the Shapiro Wilk Test, Q-Q plots, and histograms. Frequencies [number (N), %] are presented for counted (N falls, N adverse events if any, N of home exercises) and nominal data (gender, stroke etiology and location, and rehabilitation facility). Medians (interquartile range) are reported for ordinal data (mRS, BBS, FGA, TCT, FES-I, FRT, EQ-5D-3L, SARA, and SINGER), and mean (SD) is reported for continuous data (age, time after stroke, TUG, and posturography outcomes).

The significance level is defined by a two-tailed *p*-value of <0.05. Baseline (T0) between-group differences are evaluated using Fisher's exact test for nominal data, Mann Whitney-*U*-test for ordinal data and independent samples *t*-test for continuous data. If the distribution is non-normal in continuous data, data transformation or non-parametric statistics are performed, as appropriate. To evaluate within-group differences between T0, T1, and T2 measures, for ordinal data, Friedman test is utilized followed by Dunn's multiple comparisons test for pairwise comparisons. To examine between-group differences, using newly created variables (T1 or T2 minus T0 values), a Mann Whitney-*U*-test is performed. For continuous data, test assumptions for a repeated-measures analysis of variance (ANOVA) are checked (e.g., normality, sphericity) and dealt with as appropriate. If the requirements are met, repeated measures ANOVA are performed, with “time” (T0, T1, and T2 measurements) as the within-subject factor, “group” (IG, CG) as the between-subject factor, and adjusted for the stratification variables (age, sex). If statistical significance is present, a *post-hoc* analysis of pairwise comparisons between measurement time points is performed, followed by a *post-hoc* Bonferroni correction for multiple comparisons. An intention-to-treat analysis is performed analyzing all study participants in the groups which they have been assigned to.

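### For TUG and posturography the plan names no IG-versus-CG estimate: T0 is an outcome level and the only follow-up compares time points

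*Protocol article*

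**What the plan says.** Section 2.7 of the protocol article sorts outcomes by scale type. The continuous class is "continuous data (age, time after stroke, TUG, and posturography outcomes"), so the outcomes in it are TUG and posturography. If the assumptions hold, these go into a repeated-measures ANOVA with time ("T0, T1, and T2 measurements) as the within-subject factor") and with group "as the between-subject factor, and adjusted for the stratification variables (age, sex"). The T0 value is not among the adjustment variables.

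When something is significant (the text does not say which effect), the follow-up is that a post-hoc "analysis of pairwise comparisons between measurement time points is performed", with Bonferroni correction. No group-by-time term and no IG-versus-CG contrast at T1 or T2 is mentioned.

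The ordinal outcomes do get a between-group analysis: "To examine between-group differences, using newly created variables (T1 or T2 minus T0 values"), a Mann-Whitney U test is used. That sentence follows the ordinal within-group rule and precedes the continuous rule. It could reach TUG and posturography only through the fallback: "If the distribution is non-normal in continuous data, data transformation or non-parametric statistics are performed, as appropriate".

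The trial's purpose, in section 2.1, is comparative: "The aim is to investigate the effects of coordination exercises compared to standard physiotherapy, on balance and walking".

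**The concern.** The trial asks whether IG does better than CG. For TUG and posturography, the one follow-up that the plan commits to answers a different question, namely whether patients change between visits. Section 3 itself notes that these acute patients recover rapidly, so a significant time effect is to be expected in both arms. Followed as written, the analysis could report Bonferroni-corrected T0-to-T1 improvements that are silent on the treatment comparison. Section 3 also places the main interest in T0 to T1, yet no T1 group difference is specified for these outcomes.

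Having T0 as an outcome level adds to this. At T0 randomised groups differ only by chance, so a group main effect averaged over three visits includes one visit with no treatment effect. TUG is one of two outcomes labelled as walking in Table 3, and posturography is one of the balance outcomes, so both serve the stated aim.

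**Working it through.** **The plan's own figure.** Section 2.6 sizes the trial on BBS change and gives no figure for TUG or posturography.
- Difference: 17.33 − 13.67 = 3.66.
- Pooled SD: √((2.08² + 4.73²)/2) = 3.654. Inflated SD: 3.654 × 1.442 = 5.269.
- n per group = 2 × (1.960 + 0.842)² × 5.269²/3.66² = 32.5, so 33, or 66 in total as stated.
- The standardised effect is 3.66/5.269 = 0.695. It is borrowed below only as a convenient size.

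**Assumptions not in the documents.** The TUG or posturography effect is δ = 0.695 SD at both T1 and T2. Visits have unit variance and equal correlation ρ (compound symmetry). There are 33 per group and no missing data. Results are shown for ρ = 0.3, 0.5 and 0.7.

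**Group main effect.** The group differences at T0, T1 and T2 are 0, δ and δ. Their mean is (2/3)δ = 0.463 SD. The variance of a patient's three-visit mean is (1 + 2ρ)/3.

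**Group-by-time interaction.** The centred differences are −2δ/3, δ/3 and δ/3, with sum of squares (2/3)δ². The noncentrality is (n/2)(2/3)δ²/(1 − ρ), on 2 df.

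**ANCOVA at T1 adjusted for T0.** The noncentrality is (n/2)δ²/(1 − ρ²), on 1 df.

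The ratio of interaction to ANCOVA noncentrality is (2/3)(1 − ρ²)/(1 − ρ) = (2/3)(1 + ρ), that is 0.87, 1.00 and 1.13. The same ratio holds for an effect at T1 only, because the centred sum of squares is again (2/3)δ². The interaction spends 2 df where ANCOVA spends 1.

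**Simulated power** (1,500 runs per setting, two-sided 0.05):

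| Test | ρ = 0.3 | ρ = 0.5 | ρ = 0.7 |
|---|---|---|---|
| Group main effect | 0.70 | 0.60 | 0.53 |
| Group-by-time interaction | 0.68 | 0.82 | 0.98 |
| ANCOVA at T1 | 0.82 | 0.88 | 0.98 |

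Power computed from the formulas above with noncentral t and F distributions agrees to within about 0.03. The mean simulated estimate was about 0.46 SD for the group main effect and 0.69 SD for ANCOVA. The T1 − T0 change contrast also averaged about 0.69 SD, so it is unbiased. Under no effect and complete data, the interaction rejected in 0.045 to 0.051 of runs, so it holds its size.

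**Need for a T0 value.** TUG is scheduled at T0 (Table 1). Section 2.3.2 reads "Exclusion criteria are a modified Rankin Scale (mRS) score of 5 or more", so mRS 4 can enter, and section 2.3.1 sets a BBS ceiling of 47 with no floor. Some patients may therefore be unable to do a TUG at T0. Classical repeated-measures ANOVA needs a value at every visit, and a model with T0 as covariate needs a T0 value. The documents do not say how many patients this concerns. As an illustration only, if the 30% with the worst T0 values were lost, 46 of 66 would remain and ANCOVA power would be 0.66/0.75/0.90.

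**The case against.** The strongest reply is that a design with time within subjects and group between subjects conventionally contains the interaction, and that a condensed article need not write it out. That stands. A reader might infer that the analysis never estimates the treatment effect, but the documents do not support this: nothing excludes the interaction, and it validly tests differential change. What remains is that the plan does not name it as the treatment test, and that a 2-df test over three visits gives no size, direction or visit.

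A reader might also infer a very large loss of information by setting the group main effect against ANCOVA. The relative efficiency is (4/9)(1 − ρ²)/((1 + 2ρ)/3), which is 0.62, 0.39 and 0.18 at ρ = 0.4, 0.6 and 0.8, a loss of 38% to 82%. That applies only if the group main effect is read as the treatment test, which section 2.7 does not say. Against the interaction, the cost is modest to nil.

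It is equally tempting to say that patients untestable at T0 are dropped. The article states no such exclusion, declares intention-to-treat for all participants, and may leave missing-data rules to a fuller document. The possibility is real, but it is an inference without a count, and ANCOVA with a T0 covariate would share it.

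Finally, the fallback could bring in the Mann-Whitney test on change, but only if distributional assumptions fail. These are also secondary outcomes, and walking is covered by the Functional Ambulation Categories as well.

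**Conclusion.** The point holds in a limited form. For TUG and posturography, section 2.7 fixes a model with T0 as an outcome level and a follow-up that compares visits, and it specifies no between-group estimate at T1 or T2. The ordinal outcomes do get a between-group comparison.

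If the interaction is used, the power deficit against ANCOVA at T1 is about 0.14 at ρ = 0.3, 0.06 at ρ = 0.5 and nil at ρ = 0.7. If the group main effect is used, the estimate shrinks to two thirds of the truth. These sizes rest on the assumed 0.695 SD effect, equal at T1 and T2, on compound symmetry and on complete data.

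The larger defect is interpretive: the named output cannot answer the comparative question. The wording should be changed. The primary BBS comparison, which is classed as ordinal and tested between groups on change, and the sample size are not affected.

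**What to change.** Replace the repeated-measures ANOVA for TUG and posturography with a model of the T1 and T2 values that has the T0 value, age stratum and sex as covariates and includes group, visit and group-by-visit. Name the between-group difference with 95% CI at T1 as the main result and the one at T2 as the second. Between-time-point tests may stay as description but should not be presented as evidence of a treatment effect.

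Because this model also needs a T0 value, add a supporting rank-based comparison of TUG between groups at T1 and at T2, with patients unable to perform the test ranked worst. It uses no T0 value and so keeps patients who could not be tested at entry. State that the covariate-adjusted model is the analysis of record.

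The cost is analysis wording only, since the T0 values are already collected. The one downside is that the rank-based comparison gives a less intuitive effect measure.

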### 2.6 Sample size calculation

The sample size was estimated using the primary outcome data obtained from a pilot study (*n* = 7) conducted for this RCT (Meier et al., 2021), taking into account a correction for small samples. Based on a mean change in BBS score of 17.33 points (SD 2.08) in the IG and 13.67 points (SD 4.73) in the CG, the mean between-group difference and pooled SD were calculated and a correction for small samples was applied (pooled SD^*^1.442; Vickers, 2003). Using an independent samples *t*-test, power of 0.8, alpha of 0.05 and 1:1 allocation ratio, a sample size of 66 participants, 33 per group, was evaluated (HyLown Consulting LLC, 2022). Considering an attrition rate of 15%, the aim is to include 77 participants.

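### The plan promises an intention-to-treat analysis of every participant, but its named tests drop patients without T1 (primary BBS contrast) or without all three visits (Friedman, ANOVA), with 15% attrition expected

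*Protocol article*

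**What the plan says.** On the analysis population, section 2.7 (Statistical analysis) says: "An intention-to-treat analysis is performed analyzing all study participants in the groups which they have been assigned to". That sentence makes two promises: everyone is analysed, and everyone is analysed in the assigned arm.

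The same section names the tests:

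- **Ordinal outcomes, which include the primary BBS.** Arms are compared by a Mann-Whitney test "using newly created variables (T1 or T2 minus T0 values"). Change within each arm is tested by a Friedman test over T0, T1 and T2.
- **Continuous outcomes (TUG, posturography).** "If the requirements are met, repeated measures ANOVA are performed", with the three visits as the within-subject factor and adjustment for age and sex.

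On expected loss, section 2.6 (Sample size calculation) says: "Considering an attrition rate of 15%, the aim is to include 77 participants". The figure before inflation is "a sample size of 66 participants, 33 per group, was evaluated". The Discussion (section 3) places the primary objective at the change from T0 to T1.

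**The concern.** A rank test on a change score can use only patients who have both values. A Friedman test, and repeated-measures ANOVA in its standard form, can use only patients with all three visits. Unless a further step fills the gaps, each outcome analysis therefore covers fewer patients than the population sentence claims, and the number differs between tests.

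Two things are at stake. First, a reader of the report would take the primary result to include every randomised patient when it does not. If loss before T1 differs between arms and is related to recovery, the comparison is biased. That attendance might depend on recovery is an inference. The document describes rapid recovery in these patients, variable transfer timing and different assessment sites for T1 and T2, but does not say why patients would be lost. Second, for TUG and posturography, observed T1 data are discarded for any patient who does not return for T2.

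**Working it through.** **1. The plan's own figure.** Inputs are from section 2.6: "mean change in BBS score of 17.33 points (SD 2.08) in the IG and 13.67 points (SD 4.73) in the CG"; "a correction for small samples was applied (pooled SD^*^1.442"); "power of 0.8, alpha of 0.05 and 1:1 allocation ratio".

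- Difference: 17.33 − 13.67 = 3.66.
- Pooled SD, equal weights: √[(2.08² + 4.73²)/2] = 3.654. Corrected: 3.654 × 1.442 = 5.269.
- n per arm = 2 × [5.269 × (1.960 + 0.842)/3.66]² = 32.5, rounded up to 33, so 66 in total. This reproduces the plan (the exact t calculation gives 34 per arm).
- Inflation: 66/0.85 = 77.6. The stated 77 is within rounding.

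**2. Expected loss.** 77 × 0.15 = 11.55, so 11 to 12 patients, leaving 77 × 0.85 = 65.5, in effect the 66 powered for.

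**3. What each named test can use**, with no imputation:

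| Test | Outcomes | Visits needed | Patients kept of 77 |
|---|---|---|---|
| Baseline comparisons | all measured at T0 | T0 | all with T0 |
| Mann-Whitney, T1 − T0 | BBS (primary) and other ordinal | T0, T1 | about 66 to 73 |
| Friedman, within arm | ordinal | T0, T1, T2 | about 66 |
| Repeated-measures ANOVA | TUG, posturography | T0, T1, T2 | about 66 |

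The range in the second row comes from the timing of dropout, which section 2.6 does not give:

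- Assumption A, all dropout by T1: 11 to 12 lost, about 66 kept.
- Assumption B, constant dropout rate over 12 weeks: the proportion lost by week 4 is 1 − 0.85^(4/12) = 0.053, so 77 × 0.053 = about 4 lost and 73 kept.

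**4. Possible bias in the BBS contrast.** If a proportion p of an arm is lost and those patients would have gained g points less than the rest, the arm's true mean is (1 − p) × M + p × (M − g) = M − p × g, where M is the mean of those observed. The observed mean is too high by p × g. The bias in the group difference is p × g in the intervention arm minus p × g in the control arm, which is zero when loss is the same in both.

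The documents give no value for g. Taking g = 6 points as an assumption, with selective loss in one arm only:

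- p = 0.05 (near assumption B): 0.05 × 6 = 0.3 points; 0.3/3.66 = 8%.
- p = 0.15 (assumption A): 0.15 × 6 = 0.9 points; 0.9/3.66 = 25%.

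This is on the scale of means, as in the sample size calculation. It shows the order of size for a rank test, not its exact shift.

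**The case against.** The strongest reply has four parts.

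- **The primary contrast does not depend on T2.** A reader might infer that all the tests require complete T0, T1 and T2 data. They do not. The Mann-Whitney test on T1 minus T0 keeps a patient who misses only T2, and the baseline tests need T0 alone. Friedman does not compare arms, and ANOVA is used only for secondary outcomes. This part stands.
- **Silence is not exclusion.** A reader might also conclude that the whole analysis is complete-case. The article does not say that incomplete patients are removed, and imputation could be set out in the full protocol or analysis plan, which are not shown. This stands too, and the absence of an imputation rule is not the point made here. The point is that the article fixes both a population and a set of tests, and those tests alone do not deliver that population.
- **Inflating for attrition does not contradict intention-to-treat.** Correct. Going from 66 to 77 is ordinary practice and says nothing about who is analysed. It matters here only because it puts a number on the loss. Analysis as assigned is also kept by the named tests; what they do not keep is analysis of everyone.
- **The bias is hypothetical.** It rests on an assumed gap and one-sided loss. Patients who deteriorate and patients who recover fully would push it in opposite directions. This stands, so the figures are illustrations and not predictions.

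A further fair remark is that a patient with T0 only adds little to the T1 contrast under any model. The gain for BBS is a defined population and a stated assumption about missing values, more than precision.

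**Conclusion.** The point holds in a limited form. As written, the primary BBS comparison is available-case. It omits patients without T1: about 4 under constant dropout, up to 11 to 12 if all dropout comes by T1. The Friedman and repeated-measures ANOVA results are complete-case over three visits, resting on about 66 of 77 patients, and they discard T1 values from anyone missing T2. Neither matches the stated population.

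Whether this biases the group contrast depends on differential loss between arms. It is zero with like loss in both, and 0.3 to 0.9 BBS points (8 to 25% of 3.66) under 5 to 15% one-sided loss and the assumed 6-point gap. The documents do not support saying that the trial is complete-case throughout, that every test needs all three visits, or that the sample size contradicts the intention-to-treat principle.

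**What to change.** 1. **Continuous outcomes (TUG, posturography).** Replace repeated-measures ANOVA with a likelihood-based mixed model on all observed visits: group-by-time effects, age stratum and sex, unstructured covariance. T1 values from patients missing T2 are then used.
2. **BBS at T1.** Include patients without T1 through the same type of model, or keep the ordinal approach and use multiple imputation before the rank test. Name one of these as primary.
3. **Sensitivity.** Add a delta-adjusted analysis for missing T1 in which the assumed shortfall is varied over a range set in advance and may differ between arms.
4. **Labels.** Report the unimputed Mann-Whitney result as available-case and the Friedman and ANOVA results as complete-case, all as supportive, with the number analysed per arm. If the full protocol or analysis plan already sets out how patients without T1 enter the BBS comparison, a cross-reference to it may settle item 2.

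The cost is a change of wording and modest programming in R or SPSS, both already named, with no new data. It should be made before unblinding, which section 2.3.3 places after study completion; if made later, it should be reported as such. The downsides are reliance on missing-at-random, which item 3 tests, and, for a Gaussian model of BBS, an interval-scale assumption for a score that the plan treats as ordinal and for which the Discussion acknowledges a possible ceiling effect.

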## 3 Discussion

This is the first RCT to investigate the effects of coordination exercises in patients with post-stroke ataxic symptoms. As coordination exercises have been shown to reduce the progression of ataxic symptoms in patients with degenerative diseases (Marquer et al., 2014), and stroke guidelines highlight the limited evidence for targeted treatment of ataxic symptoms (Intercollegiate Stroke Working Party, 2023), this study aims to contribute further knowledge regarding tailored interventions in rehabilitation for stroke patients with ataxia. Building on the evidence for degenerative diseases, we hypothesize that stroke patients will experience faster recovery as well. As patients with cerebellar damage experience limitations in the procedural learning process (Molinari et al., 1997), especially trial-and-error learning, compensation must be sought to be able to learn motor tasks more efficiently. A high number of repetitions and intensive training, provided with coordination exercises for example, could be the simplest option (Kelly and Shanley, 2016). To assess the impact of the interventions on motor networks, the trial involves MRI examinations to investigate any potential changes.

However, there are also limitations to consider in this study. Firstly, the study is conducted in a rehabilitation setting where patients receive additional individualized therapies. These supplementary therapies could potentially influence the study results, making it challenging to exclusively attribute the observed effects to the specific intervention under investigation. Secondly, as the trial focuses on acute stroke patients who undergo rapid recovery, selecting a timely and appropriate balance assessment over the 3-month study period is challenging due to the potential ceiling effect. To address this concern, the researchers chose 47 points or fewer in BBS as an inclusion criterion to ensure the detection of significant changes from T0 to T1 (Stevenson, 2001) and included the FGA to demonstrate effects during the sub-acute stages (T1 to T2). This limitation is relatively minor since the primary objective of the study is to evaluate the impact of supervised therapy sessions from T0 to T1. Thirdly, the initial training of therapists conducting the interventions had to be performed online because of the COVID-19 pandemic. This adjustment in training methods may influence the delivery and consistency of the therapy sessions. However, therapists have the option to watch the recording of the training, whenever they feel it is necessary to refresh certain aspects.

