#### 2.3.1 Inclusion criteria

People who are at least 18 years of age, who experienced an acute ischemic or hemorrhagic stroke (identified by MRI/CT), and who suffer from gait ataxia are eligible, if they score at least 1 point on the items gait, stance, trunk or heel-shin-slide of the Scale for the Assessment and Rating of Ataxia (SARA; Schmitz-Hübsch et al., 2006) and 47 points or less on the Berg Balance Scale (BBS; Stevenson, 2001).

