#### 2.5.1 Primary outcome

The primary outcome is balance as assessed using the BBS (Berg et al., 1989). The BBS is considered the gold standard for evaluating balance in people after stroke (Blum and Korner-Bitensky, 2008). It comprises 14 items, and a Likert scale is used ranging from 0 to 4, depending on the patient's performance (Table 3).

**Table 3 T3:** Outcomes, assessments, and timepoints.

**Outcome**	**Assessment**	**T0^a^**	**T1^b^**	**T2^c^**

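### The BBS entry limit of 47 leaves as little as 9 points of headroom, less than either planned mean gain, so it does not secure the T0–T1 contrast, and an unadjusted change-score test makes the ceiling worse

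*Protocol article*

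**What the plan says.** Section 2.3.1 admits patients with "47 points or less on the Berg Balance Scale". Section 2.5.1 describes the scale: "It comprises 14 items, and a Likert scale is used ranging from 0 to 4". Section 2.6 takes its effect size from a pilot of seven patients, with a "mean change in BBS score of 17.33 points (SD 2.08) in the IG and 13.67 points (SD 4.73) in the CG". It then widens the SD ("a correction for small samples was applied (pooled SD^*^1.442") and arrives at 33 per group from a t-test with "power of 0.8, alpha of 0.05 and 1:1 allocation ratio".

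Section 2.7 lists BBS among the ordinal outcomes. For these, the between-group comparison is a Mann-Whitney U test on T1 or T2 minus T0, with no baseline adjustment stated for that test.

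Section 3 names the ceiling effect, says that "the researchers chose 47 points or fewer in BBS as an inclusion criterion to ensure the detection of significant changes from T0 to T1", adds the Functional Gait Assessment for T1 to T2, and rates the limitation as relatively minor because the primary objective concerns T0 to T1.

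**The concern.** T0 to T1 is the interval in which the planned gains have to fit on the scale, so naming it as the primary interval is no reassurance about the ceiling. If many patients enter near the limit, both arms run into the top score and the observed difference shrinks toward zero. A null result could then reflect the scale rather than the exercises.

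The planned test adds to this. On raw change scores, a patient who recovers fully from 47 (+9) ranks below one who moves from 20 to 30 (+10). The size of a change therefore depends partly on where the patient started, and the test does nothing to remove that.

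**Working it through.** **Reproducing the plan's figure (Section 2.6 inputs).**
- Difference: 17.33 − 13.67 = 3.66.
- Pooled SD: √[(2.08² + 4.73²)/2] = 3.654. Inflated: 3.654 × 1.442 = 5.269. Standardised difference: 3.66/5.269 = 0.695.
- n per group = 2 × (1.960 + 0.842)² / 0.695² ≈ 32.5, so 33, as stated. Power at 33 is 0.806 by the normal formula and 0.794 by the exact t-test. The sample size arithmetic is sound on its own inputs.

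**Headroom (Sections 2.3.1 and 2.5.1).**
- Maximum: 14 × 4 = 56. Headroom at the limit: 56 − 47 = 9.
- Highest entry score that leaves room for the control mean: 56 − 13.67 = 42.33. For the intervention mean: 56 − 17.33 = 38.67.
- Entry at 39–42 therefore excludes the intervention mean gain, and entry at 43–47 excludes both.

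**Expected difference at a given entry score.** Assume that gains are normal with SD s = 5.269, independent of baseline, and capped at headroom h. The mean observed gain is μΦ(z) + h[1 − Φ(z)] − sφ(z), with z = (h − μ)/s.
- Entry 47 (h = 9): control 8.46, intervention 8.87, difference about 0.4.
- Entry 40 (h = 16): control 12.53, intervention 14.50, difference about 2.0.
- Entry 30 (h = 26): difference about 3.6, so almost no loss.

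**Power over a baseline mix.** The article gives no baseline BBS distribution, so these are assumptions: T0 normal, truncated to 0–47; 33 per group; gains as above; T1 capped at 56. All are simulated.

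| Assumed T0 mean (SD) | Mann-Whitney on change | ANCOVA of T1 on T0 |
|---|---|---|
| 15 (no material ceiling) | 0.77 | – |
| 25 (10) | 0.75 | – |
| 30 (10) | 0.69 | 0.73 |
| 35 (8) | 0.63 | 0.69 |
| 40 (6) | 0.51 | 0.64 |

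The first row matters for reading the rest. With no material ceiling the Mann-Whitney test already gives 0.77, so about 0.03 of any shortfall from 0.8 belongs to the change of test. In the last row 44% of patients score 56 at T1.

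**Two alternative assumptions that remove or reduce the loss.**
- If the latent gains are set so that the capped, observed means equal 17.33 and 13.67, Mann-Whitney power is about 0.80 to 0.85 at T0 means 25 to 35.
- If the pilot's own pooled SD (3.65) replaces the inflated one, the capped model gives 0.96, 0.94, 0.89 and 0.73 at T0 means 25, 30, 35 and 40.

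**The case against.** The strongest counter-argument concerns power. A reader might infer from the 9-point headroom that the stated 0.8 power is not delivered. The article does not support that. Forty-seven is an upper limit, not a typical score; the assumed gains are group means; and no baseline distribution is given for the pilot or the trial. The pilot gains were also observed on the same 0–56 scale, so they already carry whatever ceiling the pilot had, and capping them again may count it twice. A shortfall through the ceiling requires the trial's patients to have less room, relative to their gains, than the pilot's. The SD of 5.27 is itself a deliberate safeguard. All of this stands.

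Nor does the planned difference vanish in every higher-scoring patient: at entry 40 about 2.0 of the 3.66 points remain.

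It can also be said that Section 3 discloses the ceiling, and that its sentence may mean change over time rather than the between-group difference. Disclosure is to its credit. But even on the change-over-time reading, a 9-point maximum gain is below both planned means, and the rating as minor rests on naming the very interval in which those gains must occur.

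Finally, ceiling models are details that an unseen analysis plan may hold. That is fair for a censored model. The unadjusted Mann-Whitney test on change scores, however, is fixed in Section 2.7.

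**Conclusion.** The concern holds as a mismatch between the entry limit, the planned gains and the reassurance in Section 3. The cut-off does not secure detection of the planned T0–T1 difference in patients entering above about 38 to 42, and the rating as relatively minor does not follow from the plan's own figures.

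The effect on power is conditional. It is negligible if most patients enter at about 25 or below, or if observed gains match the pilot's. It is material, with Mann-Whitney power about 0.5 to 0.7, if baselines centre at 30 to 40 and the inflated SD applies. These ranges assume normal gains, equal SDs, gain independent of baseline, a hard cap at 56, and that the pilot changes refer to T0–T1, which Section 2.6 does not state.

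The choice of test is the part worth changing whichever baseline mix applies. Under the planned gains, adjustment for T0 BBS does as well as or better than the change-score test in nearly every scenario, and it helps most where the ceiling bites: 0.63 to about 0.7 at mean 35, and 0.51 to 0.64 at mean 40.

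**What to change.** Keep the entry rule, and make three changes.

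1. **Section 2.7.** Before unblinding, replace the between-group test for BBS with a baseline-adjusted analysis of T1 BBS: proportional odds, or ANCOVA, with T0 BBS as covariate. A model treating 56 as right-censored belongs in a sensitivity analysis only, because it leans on a distributional assumption. A supportive analysis in patients with T0 BBS of 38 or below is optional.
2. **Section 2.6.** State that the 0.8 power assumes no ceiling beyond the one already in the pilot, and give the range of power under the blinded pooled T0 BBS distribution with the cap at 56.
3. **Section 3.** Soften the claim that the cut-off ensures detection and the rating of the ceiling as relatively minor.

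The cost is analysis wording and one blinded calculation. T0 BBS is already collected, and no patients or visits are added. The stated power may look less favourable. Section 4 planned completion by the end of June 2024, and Section 2.3.3 places regular unblinding after completion. If unblinding has already taken place, the planned test should stay primary and the adjusted analysis should be reported openly as added later.
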